## Abstract

**Background:**

Serious mental illness (SMI) affects 4.6% of the American population. While treatments are available, adherence to specific regimens is often suboptimal. Multiple organizations, such as the Substance Abuse and Mental Health Services Administration (SAMHSA), have called for more options that improve accessibility and engagement to treatment among individuals with SMI. This study protocol answers such calls by testing the effectiveness of peer specialists—individuals with SMI trained to use their experience to help others with SMI—in delivering social skills training (SST) and cognitive behavioral social skills training (CBSST), evidence-based treatments effective at engaging individuals with SMI to make behavioral and cognitive changes. Peer specialists have been shown to be adept at engaging those with SMI in treatment; however, their ability to deliver these structured treatments is unknown.

**Methods:**

This study is a randomized, hybrid 1, research assistant-blinded, superiority trial. A total of 252 veterans with SMI will be recruited and randomized to one of three arms: CBSST-Peer vs. SST-Peer vs. treatment as usual. Participants randomized to CBSST-Peer or SST-Peer will participate in a 20-week group-based intervention that meets weekly for a 60-min class. All participants will complete 4 study assessments at baseline, 10 weeks, 20 weeks, and 32 weeks. A multidimensional battery of functional outcomes will be used with the Independent Living Skills Survey (ILSS) as the primary outcome measure. Post-study completion, veterans who participated in the CBSST-Peer or SST-Peer arms will randomly be invited to participate in focus groups, and peer specialists will complete interviews to further assess the effectiveness of each intervention.

**Discussion:**

Improving care and outcomes for individuals with SMI is a national priority. To improve care, it is imperative to think about new ways to improve engagement and accessibility to care. This study provides an innovative solution to this problem by evaluating how two different types of treatment, delivered by peer specialists, compare to usual care. The results of the study will allow for the expansion of treatment options that improve access and engagement among veterans with SMI.

**Supplementary Information:**

The online version contains supplementary material available at 10.1186/s13063-022-06376-9.

## Background

Serious mental illness (SMI) encompasses many mental, behavioral, or emotional disorders that result in serious functional impairment and affects 11.4 million (4.6%) US adults aged 18 or older [1]. Treating SMI is often complicated. Medications can be effective in treating two hallmark symptoms—hallucinations and delusions; however, when solely used to manage illness, rates of non-adherence increase over time [2]. Those with SMI often have difficulty accessing care and often drop out. Due to the complicated nature of treatment and barriers to care, the Interdepartmental Serious Mental Illness Coordinating Committee, led by the Substance Abuse and Mental Health Services Administration (SAMHSA), called for enhanced efforts across five areas to improve care for those with SMI [3]. The second and fifth foci aim at improving access and engagement in care. Recommendations for better access to and engagement in care include the use of peer supports (i.e., individuals with SMI helping each other) and cognitive therapies (improving errors in thinking) and a movement towards understanding what is most effective. More research is needed to understand how best to use peer support to improve access to and engagement in care. This study offers an opportunity to fill the gaps in knowledge around peer support and effective behavioral and cognitive treatments.

Peer specialists—a particular type of peer support—are individuals in recovery from SMI who receive specialized training and use their lived experience to support others with SMI [4]. Peer specialists often collaborate with professionally credentialed mental health care providers to extend care beyond more traditional settings [5]. While peer specialists have been shown to contribute to improved care access and engagement among those with SMI, they are not credentialed to provide a full range of treatment. For this reason, research has focused on how to maximize the services they can provide. Chinman et al.’s [4] literature review of 20 studies showed that peer support services are especially effective when they use structured goal-setting curricula. One particular curriculum, cognitive behavioral social skills training (CBSST), provides an important opportunity to test peer specialists’ effectiveness in delivering a structured curriculum for patients with SMI.

CBSST [6] was developed by combining techniques derived from cognitive behavioral therapy (CBT) and social skills training (SST), including thought challenging, role-playing of communication skills, and problem-solving training, into a unique intervention that enhances daily role functioning. CBSST is a recovery-oriented psychosocial rehabilitation intervention that helps patients with SMI set goals, corrects errors in thinking, and builds communication skills to improve social functioning [7]. CBSST studies have demonstrated improved functioning, negative symptoms, and defeatist attitudes among individuals with schizophrenia and psychosis [7–13]. In these studies, CBSST was delivered by masters- or doctoral-level therapists, which limits how widely the intervention can be delivered.

Testing CBSST delivery by peer specialists provides several benefits. If effective, more providers will be able to deliver the intervention in a clinical setting, which meets SAMHSA’s third focus area. Additionally, peer specialists have the unique opportunity to use their lived experience while delivering the intervention which can enhance engagement among participants. Furthermore, this structured interface with SMI participants provides peer specialists with an ideal format to assist participants with achieving and maintaining recovery while improving functioning.

A recent pilot study using peer specialists to deliver CBSST showed improvement in outcomes among participants with SMI (*n* = 12) and demonstrated the ability of the peer specialists to deliver CBSST with high fidelity [14]. This study is the next step to examining the effectiveness of CBSST among individuals with SMI while also assessing implementation considerations in typical clinical settings. This study tests the effectiveness of peer specialists delivering CBSST (called CBSST-Peer) compared with SST-Peer and usual care among a population of veterans with SMI. Social skills training (SST) is another curriculum that targets some of the same social skills as CBSST but does not target errors in thinking (the “cognitive” in CBSST). Two meta-analyses of 49 SST clinical trials of patients with schizophrenia show that SST can improve basic conversation skills and community functioning [15, 16]. The following specific aims were developed based on the results of the pilot study.

### Study aims

The following are the study aims:Compare the impact of CBSST-Peer on outcomes in veterans with SMI to veterans receiving SST-Peer and treatment as usual (TAU)Use focus groups with study participants and interviews with peer specialists and other staff to assess perceptions of SST- and CBSST-Peer and identify the potential barriers and facilitators to future implementation

To date, no study has tested peer-delivered SST or CBSST or compared the two in a rigorous trial. Should this study show that either of these manualized treatments delivered by peer specialists are effective, it could increase the availability of evidence-based services veterans could receive.

## Methods

### Study design

This is a randomized, hybrid 1, research assistant (RA)-blinded, superiority trial involving 252 veterans with SMI from one Mid-Atlantic VA Medical Center comparing three arms: CBSST-Peer vs. SST-Peer vs. TAU. Hybrid 1 trials test the effectiveness of an intervention and collect implementation barriers and facilitators that could inform its future adoption [17].

After participants are randomized, they will be followed for 32 weeks—baseline, 10-week, 20-week, and 3-month post-intervention assessments (see Fig. 1). All research activities have been reviewed and approved by the Veterans Administration Central Institutional Review Board (IRB) and reviewed by local IRBs and Research & Development Committees. Participants will provide written informed consent at the first study visit. RAs will inform the participants about the reasons the research is being done, the study procedures, and the risks and benefits. Participants are encouraged to ask questions and must demonstrate their understanding of the study by passing a brief quiz prior to signing the consent. As part of the consent, participants are asked if they are willing to be contacted later about participation in a focus group. Significant study changes will be communicated to the participants by reconsent if necessary.

**Fig. 1 Fig1:**
[figure not shown]
SPIRIT figure

### Recruitment

Recruitment for this study takes place via a combination of IRB-approved advertisements placed throughout the VA Medical Center, provider referrals, and review of VA medical records via the VA’s Corporate Data Warehouse (CDW) using ICD10 codes of SMI diagnosis of interest to assess eligibility.

### Participant eligibility

The following inclusion criteria, selected to increase generalizability, will be used: (1) age 18 and older; (2) primary diagnosis of SMI documented in the medical record (schizophrenia, schizoaffective disorder, bipolar disorder with psychotic features, major depression with psychotic features, delusional disorder, schizophreniform disorder, another specified schizophrenia spectrum, and other psychotic disorders); and (3) fluency in English. The exclusion criteria are as follows: (1) medication changes in the prior month; (2) significant current or recent (within the past year) CBSST or SST; (3) level of care at baseline that interferes with outpatient participation; (4) current hospitalization for psychiatric, substance use, or physical illness; (5) inability to pass a screening for cognitive impairment [18] during informed consent process; (6) inability to pass the 10-item T/F quiz about the details of the study informed consent, (7) current pregnancy; and (8) current incarceration.

Veterans will continue to receive ongoing care with their current providers, which for this population typically includes medication management, case management, and occasional psychotherapy targeting disorder-specific symptoms. This treatment will continue independent of the study, and no one involved in the study will make decisions regarding pharmacotherapy or other behavioral health treatments for the veteran. Participants will be withdrawn if they demonstrate a repeated pattern of non-participation and indicate they are no longer interested or do not respond.

### Randomization procedures and rationale

Once veterans are enrolled and have completed the baseline assessment, block randomization will be performed using a computer-generated list of numbers with a centralized web-based database system (Daciforms; Dacima Software Inc., Montreal, QC). RAs will use the database, set on the blinded status, to randomize enrolled participants once all prescreening information has been entered. Although veterans and the peer specialists will know to which condition the veterans have been assigned, RAs responsible for all assessments will be blinded to the study treatment assignment to prevent bias with subjective data collection measures in subsequent assessments. Data analysts will also be blinded.

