### Peer specialists

Peer specialists will be VA employees who are hired using the VA’s national guidelines for peer specialists, which specify the qualifying mental health conditions. These guidelines state that “a serious mental illness like schizophrenia, bipolar disorder, major depression, depression and anxiety disorders, post-traumatic stress disorder (PTSD), and substance use disorders qualify” [34]. Peer specialists will receive a full-day training in CBSST-Peer from CBSST experts. Part of the training involves developing their own examples to demonstrate the skills to be taught. For SST-Peer, each peer specialist must complete a 4-h online training course and pass the evaluation test. Then, an SST Master Trainer will hold a full-day training. After that, using audio tapes, the peer specialists will be evaluated and mentored over 6 months on their fidelity to the SST model. Peer specialists will receive weekly supervision on both interventions.

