### Analyses

#### Statistical analyses

Primary analyses will use hierarchical linear models (HLMs) for continuous variables. The HLMs will include random person-level intercepts and random time slopes. Possible random effects for cohort and peer specialist heterogeneity will be explored. Analyses will include all available data with maximum likelihood estimation, which is preferred over multiple imputations. All tests will be two-sided with alpha = 0.05.

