##### Aim 1: Effectiveness analysis and hypothesis

Analyses will test our hypothesis that veterans in CBSST-Peer will have superior functioning, recovery, attitude, and skill knowledge outcomes during treatment and follow-up relative to veterans in SST-Peer or TAU, and further that veterans in SST-Peer will have superior outcomes relative to TAU. Secondarily, we will apply all analyses to the symptom measures and explore the impact of gender and racial/ethnicity status where sample size allows. Analyses will follow the same pattern for all the above assessments. We will examine scores obtained at weeks 10 (mid-intervention), 20 (end-of-intervention), and 32 (post-intervention follow-up) as the outcome in HLM, with treatment condition included as a time-invariant covariate, and random intercepts for person and random slopes for time. All available data will be included in accordance with maximum-likelihood estimation procedures with data assumed missing-at-random, an assumption that will be tested with baseline clinical and demographic data. Preliminary analyses will examine potential baseline differences between the three conditions. Relevant covariates including treatment attendance, baseline symptom severity (via BPRS, CAINS), care services, and medications received (standard variables from the PSR toolkit), and demographic variables will be tested and included in the overall model according to model fit. The primary analysis will compare CBSST Peer to SST-Peer and TAU with independent contrasts in the HLM model of all post-baseline time points, to directly test the primary hypothesis that CBSST-Peer has superior outcomes than the other treatments (we will also compare SST-Peer to TAU). As compared to the group by time interaction, this test typically has greater power and is less susceptible to sample-specific artifacts (e.g., regression to the mean, variability in change over time). However, we also wish to examine the degree of change in outcomes over time in CBSST-Peer vs SST-Peer vs TAU. Thus, we will conduct additional analyses to test the treatment condition × time interaction, to examine the question of whether CBSST-Peer has greater improvement in outcomes over time than the other treatments.

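### The stated blinding of data analysts cannot hold for the two TAU contrasts, because the primary model is built by testing treatment attendance and exploring peer-specialist effects, which TAU veterans do not have.

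*Protocol article*

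**What the plan says.** Under Randomization procedures and rationale, after describing the blinding of the research assistants, the article adds: "Data analysts will also be blinded". It does not say what the analysts are blinded to, or until when.

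The analysis sections then describe how the model is reached:

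- Aim 1 (effectiveness analysis) lists the candidates: "Relevant covariates including treatment attendance, baseline symptom severity (via BPRS, CAINS), care services, and medications received", together with demographic variables. These "will be tested and included in the overall model according to model fit".
- The same section gives that model's purpose: "The primary analysis will compare CBSST Peer to SST-Peer and TAU with independent contrasts in the HLM model of all post-baseline time points". SST-Peer is also to be compared with TAU.
- Statistical analyses adds: "Possible random effects for cohort and peer specialist heterogeneity will be explored".

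The abstract shows which arms have classes: "Participants randomized to CBSST-Peer or SST-Peer will participate in a 20-week group-based intervention that meets weekly for a 60-min class". Nothing of the kind is described for TAU. On the leaders, the Peer specialists section says: "Peer specialists will receive weekly supervision on both interventions".

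**The concern.** Coding the arms A, B and C masks an analyst only if no other field gives an arm away. Session attendance and class leader do so for TAU. The Aim 1 list names attendance separately from care services, so the natural reading is attendance at the study classes, which a TAU veteran cannot have. Anyone who tests attendance or a leader effect as a model term therefore sees one coded arm with neither.

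This matters because the model is not fixed in advance: covariates are kept by fit and random effects are explored. Analyst blinding is the protection that the article offers against choosing a model with the result in view. It fails for CBSST-Peer versus TAU, which is part of the primary hypothesis, and for SST-Peer versus TAU. The same rule also lets a post-randomisation variable into the model that carries the primary contrasts.

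**Working it through.** No published figure is at issue here, so there is none to reproduce. The check has three steps.

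**1. Can TAU be identified?** Inputs: 252 veterans in three arms, so 84 per arm if equal; classes in two arms only. Assumption, since the article gives no figure: a share q of 5% to 30% of class-arm veterans never attends.

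- By arm, with coded labels: a class arm looks like TAU only if all 84 members have no sessions, with probability q^84. At q = 0.30, log10 = 84 × log10(0.30) = -43.9, about 10^-44. At q = 0.05 it is -109.3. TAU is identified with practical certainty.
- By person, without any label: P(TAU | no sessions) = 84 / (84 + 168q). This gives 0.91, 0.83, 0.71 and 0.63 (0.625) at q = 0.05, 0.10, 0.20 and 0.30.

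Attendance alone is enough for this. It does not separate CBSST-Peer from SST-Peer, and leader identity need not do so either, because peer specialists are supervised on both interventions.

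**2. What happens if attendance enters the model?** Take one value per person, 84 per arm, and a linear attendance term. With Δ the difference in mean sessions between a class arm and TAU, and s² the variance of sessions within a class arm (zero in TAU), the variance of the contrast with TAU is multiplied by

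1 + Δ² / (168 s² × 2/84) = 1 + Δ² / (4 s²).

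Assume 20 sessions and a person-level attendance rate with SD 0.20. If attenders have mean m and variance v, then Δ = (1 - q)m and s² = (1 - q)v + q(1 - q)m².

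- q = 0.10, mean rate 60%: m = 12; v = 20 × (0.60 - 0.36 - 0.04) + 400 × 0.04 = 20. Δ = 10.8; s² = 18 + 12.96 = 30.96. Factor 1 + 116.64/123.84 = 1.94 (simulated 1.98).
- q = 0.20, mean rate 70%: m = 14; v = 20 × (0.70 - 0.49 - 0.04) + 16 = 19.4. Δ = 11.2; s² = 15.52 + 31.36 = 46.88. Factor 1 + 125.44/187.52 = 1.67 (simulated 1.70).

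The simulation truncates attendance rates at 100%, which explains the small differences. For CBSST-Peer versus SST-Peer, with equal expected attendance, the factor is 1 + (2/84)/4 = 1.006 (simulated 1.006 to 1.007).

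The estimate moves as well. With b the fitted slope per session, the adjusted TAU contrast is the unadjusted one minus b × Δ. In the limiting case where benefit is proportional to sessions attended, b × Δ is the whole effect and the expected adjusted contrast is zero.

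**3. Is selection by fit harmful among baseline covariates?** Simulations with 3 × 84 veterans, 10 candidate baseline covariates of assumed strength and no true effect gave 4.8% to 6.3% false positives for AIC selection (Monte Carlo error about 0.6 points), against about 5% for a fixed set. Taking the most favourable of three fit criteria (AIC, likelihood-ratio test at 0.05, BIC) gave 5.9% and 6.5% in the two strength scenarios. At d = 0.35, power was 0.74 with AIC and 0.73 with the fixed set. So this part of the rule is close to nominal and costs no power.

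**The case against.** The strongest reply is that this is an article. The full protocol or an analysis plan could stage the release of data, or have the model chosen by someone without attendance and leader fields. The article does not say that the people who select covariates hold those fields at that moment. That stands as a limit: that the model is chosen with TAU visible is an inference. It does not remove the conflict, because the article states both an unqualified blinding and a procedure that defeats it, with no staging in between.

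Four stronger readings are tempting and are not supported.

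- A reader might infer that cohort exists only in the class arms. The article does not define cohort, and an enrolment wave would cover all three arms.
- A reader might infer that the thought-challenging half of the Comprehensive Modules Test unmasks CBSST-Peer versus SST-Peer. Table 1 says the total score is used, both class arms receive social-skills content, and separation would presuppose the effect under test.
- A reader might infer that lost blinding inflates the false-positive rate to 8.5% to 10.5%. That result comes from taking the smallest p-value over 15 models. An analyst with coded arms sees the same two-sided p-values, so it does not measure lost blinding, and most of the 15 models are not fit rules.
- A reader might take "Preliminary analyses will examine potential baseline differences between the three conditions" as a rule that imbalance triggers adjustment, with a loss of power. The article says only that differences are examined.

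**Conclusion.** The point holds for TAU. As written, the blinding of analysts cannot be kept for CBSST-Peer versus TAU and SST-Peer versus TAU while the primary model is built by testing attendance and exploring peer-specialist effects. For CBSST-Peer versus SST-Peer, coded labels can still mask.

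Identifying TAU is practically certain over the whole assumed range of non-attendance. It rests on attendance meaning study-class sessions and on those fields being available during model building. No inflation of the false-positive rate through lost blinding has been shown.

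The material harm under the written rule is that attendance can enter the primary model. The variance of CBSST-Peer versus TAU then rises about 1.7 to 2.0 times, so its standard error rises about 1.3 to 1.4 times (square roots), and the estimate shifts. These factors depend on the assumed attendance. They hold at a given residual variance, so any residual variance that attendance explains would offset part of the rise.

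**What to change.** 1. Before any post-baseline data are opened, fix one set of baseline-only covariates for the primary model: the baseline value of the outcome, baseline BPRS and baseline CAINS, all already collected. Fix the random-effects structure at the same time. This replaces selection by model fit.
2. Withhold attendance and leader fields from whoever builds the model until model and code are locked. If a leader term belongs to the fixed structure, write it into the code beforehand and merge the field only at the locked run.
3. Use attendance only in a separate secondary analysis after the lock.
4. Reword the sentence under Randomization procedures and rationale to say that analysts are blinded to arm until model and code are locked.

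The cost is a few sentences of protocol or analysis-plan text and a staged data release. No visit, treatment or sample size changes. The downside is that the model can no longer be tailored after the data are seen.
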